**Methods:**

This protocol is for a single-blind, parallel group randomized controlled trial comparing the effectiveness of a five-day residential workshop focusing on the use of character-strengths and subsequent 8- to 10-week remote telephonic coaching (weekly) to individually support ASHAs to improve their wellbeing, against routine health system support. The arms are intervention added to routine ASHA supervision (weekly, by the ASHA supervisor), and routine supervision alone (control arm). The target sample comprises 330 rural ASHAs in Madhya Pradesh, India. The primary outcome of mean Authentic Happiness Inventory (AHI) scores will be compared between arms at 3-month follow-up. Secondary outcomes will include an assessment of ASHA's self-reported affect, self-efficacy, flourishing, burnout, motivation, physical health symptoms, quality of life, and routine work performance indicators, and the consequent patient-level outcomes [e.g., service satisfaction and depression remission rates after receiving brief psychological treatment by trained ASHAs]. We will also evaluate the costs of developing and delivering the intervention.

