#### Primary outcome (ASHA-level)

2.4.1

Authentic Happiness Inventory (AHI) is a subjective measure for the assessment of happiness [40]. We have used the term ‘wellbeing’ to represent this specific measure of happiness (including hedonic (pleasure attainment) and eudaimonic (meaning and self-realisation) wellbeing). AHI includes 24 sets of five statements [e.g., ranging from 1 (“I feel like a failure”) to 5 (“I feel I am extraordinarily successful”)] from which, the respondent chooses the statement that best describes her feelings in the past one week. AHI has been designed for monitoring upward changes in happiness [40] and has often been used in positive psychology intervention studies [[41], [42], [43], [44]]. Internal consistency at pre-test has been reported to be high (Cronbach's α = 0.94). AHI has been validated for construct validity, and linguistically/contextually adapted for this trial. AHI will be administered at baseline, 3 months (primary outcome assessment) and 6 months (potential long-term effects on wellbeing).

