#### Secondary outcomes (ASHA-level)

2.4.2

For assessing the possible explanatory variables, which could contribute to the hypothesized between-arm difference in wellbeing/authentic happiness scores at 3-month follow-up, the 20-item international Positive and Negative Affect Schedule (PANAS) Short Form (I-PANAS-SF) will be used to assess ASHA affect [45]; the ‘Flourish index’ (by VanderWeele, T.J.) including two questions from each of the five principal domains of happiness and life satisfaction, mental and physical health, meaning and purpose, character and virtue, and close social relationships, will be used to assess flourishing [46]; and the Occupational Self Efficacy Scale (OSES) will be used to assess self-efficacy [47]. These measures will be administered at baseline, 1- and 3-months. For assessing the levels of variables related to wellbeing/authentic happiness, the emotional exhaustion sub-scale of the Maslach Burnout Inventory–Human Service Survey [48], the motivation scale pretested for Indian frontline health workers [49], the 14-item Physical Health Questionnaire [50] to assess somatic symptoms (contributed by work-stress/burnout) and the health-related quality of life survey (EQ-5D) validated for the Indian population [51] will be used at baseline, 3- and 6-months.

Daily/weekly/monthly/quarterly service delivery measures (depending on the type of service and as routinely monitored by the health system) will represent a global measure of routine ASHA services (non-mental health) in terms of their contact points with the community, for example through home visits, facility contacts, and community visits. We will categorize this outcome as per the type of services, such as proportion of antenatal check-ups, vaccinations, or post-natal care visits completed out of the expected for a defined period (e.g., month or quarter, as gathered by the health system). We will collect the service delivery data from the district team from the period starting from baseline till 6-month follow-up for between arm comparisons. We will gather data on the fidelity of the routine supervision activities from ASHA supervisors of both arms as part of data collection for secondary ASHA-level outcomes to monitor the ‘standard of care’ as discussed in section 2.3.5.1 and Table-1. Besides this aspect, there is no involvement of the health system appointed ASHA-supervisors in the study or the intervention. Refer Table 2 for details on ASHA-related outcome measures.

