**Primary Outcome**					
***Wellbeing***	Authentic Happiness Inventory (AHI)	Authentic Happiness Inventory (AHI) is a subjective measure for the assessment of happiness [40]. AHI includes 24 sets of five statements [e.g., ranging from 1 (“I feel like a failure”) to 5 (“I feel I am extraordinarily successful”)] from which, the respondent chooses the statement that best describes her feelings in the past one week. AHI has been designed for monitoring upward changes in happiness [40] and has often been used in positive psychology intervention studies [[41], [42], [43], [44]]. Internal consistency of 0.94 at pre-test has been reported.	We have used the term ‘wellbeing’ to represent this specific measure of happiness – AHI items represent both hedonic (pleasure attainment) and eudaimonic (meaning and self-realisation) wellbeing.	Mean AHI scores will be significantly greater in the intervention arm or among ASHAs receiving the character-strengths based coaching intervention in addition to routine supervision, compared to ASHAs receiving routine supervision alone (control arm)	Baseline, 3- and 6-month follow-up

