***Cost of Intervention delivery***	Cost of ASHA's participation in the workshop (survey) and cost of participation in remote coaching (survey)	We will assess costs incurred by ASHAs due to their participation in their respective intervention workshop and remote coaching activities. A post-workshop questionnaire (on day-5) and a remote coaching questionnaire (during the 4th and 8th coaching call, covering data of the previous calls) will be developed and administered to capture individual-level costs incurred by ASHAs, such as items covering their workshop/remote coaching time, workshop travel time, workshop travel costs, smartphone data packs (remote coaching) and food/refreshment costs (residential workshop).	If the primary outcome results show significant differences in mean authentic happiness scores between arms at 3-month follow-up as seen in the pilot study (under peer review), estimating the cost of delivering such an intervention will have significance from the point of view of health system adoption.	Data only collected in the intervention arm	Post-workshop questionnaire administered to ASHAs on day-5 of each intervention workshop batch.
					Remote coaching questionnaire administered to ASHAs during the 4th and 8th coaching call, covering data of the previous calls.

With respect to depression care delivery, we will calculate the number of ASHAs’ HAP sessions, on a weekly basis. At 3-month and 6-month follow-up, we will compare the numbers of these HAP sessions between arms (Note: HAP treatment durations range from 6 weeks to 3 months), in addition to numbers of patients with closed (completed) treatments and drop-outs.

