### Sample size estimation

2.6

In the absence of trials looking at the effectiveness of interventions aimed at improving wellbeing among community health workers in India, we referred to methodologically similar designs for calculating the sample size [[55], [56], [57]]. We will measure the change in wellbeing, pre- and post-intervention, in terms of mean happiness scores on the Authentic Happiness Inventory (AHI). We initially assumed a significant between-group difference of 0.19 points (effect size: 42 %) for the mean happiness scores at 3-month follow-up for the intervention arm (mean: 3.35, SD: 0.43) and control arm (mean: 3.16, SD: 0.48). With 90 % power and a two-sided α of 0.05, 122 ASHAs per arm are required to measure this difference by the independent group *t*-test.

The patient-outcome of depression severity will be measured by the nine-item Patient Health Questionnaire (PHQ-9) [32]. We will assess the proportion of patients who show ‘early remission’ or attain a post-treatment score of <10 [58] and compare these remission rates between the two arms at the patient's 3-month follow-up assessment. For the patient-outcome, we will refer the early remission rates in the PRIME Cohort study [58] due to its contextual similarity to our trial and assume rates of 40 % and 60 % in the control and intervention arm respectively. With a two-sided α of 0.05, and 80 % power, we will need 97 patients with depression per arm. Therefore, each of the 122 ASHAs per arm will be required to provide HAP sessions to at least 1 patient, accounting for dropouts from treatment and loss to follow-up.

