### Statistical analysis

2.8

All outcome analyses will be intention-to-treat using imputation of missing outcome data by an appropriate method [60]. The primary outcome analysis will estimate the difference in the mean happiness score between ASHAs randomized to the coaching intervention versus routine supervision at baseline, and 3 and 6 months thereafter. We will assess moderation of coaching effect by *a priori* moderators (e.g., ASHA's age, education status and years of community experience) by fitting appropriate interaction terms and testing for heterogeneity of coaching effects in regression models. We will also assess the relationships between ASHA-level affect, self-efficacy and flourishing, and their more extrinsic outcomes such as authentic happiness, burnout, motivation, physical symptoms and quality of life, and the relationships between these extrinsic outcomes and their service delivery measures, patient satisfaction (of patients receiving depression care) and patient depression remission rates, by a combination of descriptive analyses, statistical tests of significance, and mediation analysis using the MacKinnon's approach [61]. From a patient outcome standpoint, we will compare the remission rates on PHQ-9 of patients between the arms at 3 month follow-up using the test of difference between two independent proportions.

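### Section 2.8 spreads the primary outcome analysis over baseline, 3 and 6 months without ranking them, while the rest of the protocol makes 3 months the single primary comparison

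*Protocol article*

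**What the plan says.** Section 2.8 (Statistical analysis) is the only place that says what the primary outcome analysis estimates: the difference in mean AHI "between ASHAs randomized to the coaching intervention versus routine supervision at baseline, and 3 and 6 months thereafter". The three visits have equal standing in that sentence.

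Elsewhere the protocol settles on 3 months:

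- Abstract, Methods: "The primary outcome of mean Authentic Happiness Inventory (AHI) scores will be compared between arms at 3-month follow-up".
- Section 2.4.1: "AHI will be administered at baseline, 3 months (primary outcome assessment) and 6 months (potential long-term effects on wellbeing". This gives each follow-up visit its own role.
- Section 2.4.2 speaks of the "hypothesized between-arm difference in wellbeing/authentic happiness scores at 3-month follow-up".
- Table 2, cost row, makes the value of costing depend on the primary results showing "significant differences in mean authentic happiness scores between arms at 3-month follow-up".
- Section 2.6 sizes the trial on 3-month means (3.35 against 3.16) with an independent-group t-test.

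Two places leave the time open. The primary hypothesis in section 1.1 names no visit. The primary-outcome row of Table 2 states its hypothesis without a visit and gives the timeline as "Baseline, 3- and 6-month follow-up".

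**The concern.** The sentence that defines the primary analysis does not match the endpoint that the protocol defines elsewhere. There are two separate problems.

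First, if the 3-month and 6-month results disagree, someone could cite 2.8 to present the 6-month result as part of the primary analysis, and someone else could cite 2.4.1 against it. The analysis section should leave no room for that argument. In the same paragraph, the patient remission comparison is tied to its 3-month visit, so the lack of a single visit for AHI stands out.

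Second, the list includes baseline. Section 2.3.4 places random allocation after the baseline assessment. A baseline difference between arms arises by chance and says nothing about the coaching, so it does not belong in an analysis meant to estimate the effect of coaching.

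**Working it through.** **Step 1. Reproduce the sample size, to see which test the design was built for.**

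Inputs (section 2.6): difference 0.19; SDs 0.43 and 0.48; two-sided alpha 0.05; power 90%; stated result 122 per arm.

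- Pooled SD = √[(0.43² + 0.48²)/2] = 0.4557.
- Standardised difference = 0.19 / 0.4557 = 0.417, which matches the stated 42%.
- Normal approximation: n = 2(1.960 + 1.282)² / 0.417², which rounds up to 121 per arm.
- Exact noncentral-t calculation: 122 per arm, power 0.9004.

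The stated 122 is therefore one t-test at one visit at the full 5%. No alpha was set aside for a second primary visit.

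**Step 2. Compare the wording by section.**

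| Place | Visit for the primary AHI comparison |
|---|---|
| Abstract | 3 months |
| 2.4.1 | 3 months primary; 6 months for long-term effects |
| 2.4.2 | 3 months |
| Table 2, cost row | 3 months |
| 2.6 | 3 months |
| 1.1 and Table 2, primary row | none named |
| 2.8 | baseline, 3 and 6 months, unranked |

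Section 2.8 is the outlier.

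**Step 3. What a literal co-primary reading would cost.**

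Suppose significance at either 3 or 6 months, each at two-sided 5%, counted as success. The protocol states no such rule. With Z₁ and Z₂ the two test statistics under the null and r their correlation:

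familywise error = 1 − P(|Z₁| ≤ 1.96 and |Z₂| ≤ 1.96).

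The protocol gives no value for r, so a range is shown.

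| Assumed r | Familywise error |
|---|---|
| 0 (upper limit) | 1 − 0.95² = 9.75% |
| 0.4 | 9.3% |
| 0.5 | 9.1% |
| 0.7 | 8.3% |
| 0.9 | 7.0% |

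Splitting alpha at 0.025 per visit would control this. Power at 122 per arm would then fall to 84.1% for each visit, and 145 per arm would be needed for 90% (both by the t calculation, with the same 0.19 difference and SDs at each visit).

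**Step 4. With 3 months as the only primary visit.**

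Alpha stays at 0.05 and the requirement stays at 122 per arm. Adjusting for baseline AHI multiplies the variance of the 3-month comparison by about 1 − r_b², where r_b is the correlation of baseline with 3-month AHI. The protocol does not give r_b. For any value other than zero the factor is below 1, so 122 per arm remains enough under the stated assumptions.

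**The case against.** The strongest reply is that the primary time point is already fixed. Section 2.4.1 labels 3 months as primary and gives 6 months a different purpose, and four other places agree. The 2.8 sentence can be read as covering the primary outcome measure at every visit where it is collected. It speaks of estimating, and it names no test, alpha or success rule. Most of this stands, and it limits how far the point can be taken.

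Three stronger readings are tempting, and the protocol does not support them:

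- *A reader might infer that the trial has two primary tests, each at an unadjusted 5%.* Section 2.8 states no alpha. The only alpha given for AHI belongs to the single 3-month t-test in 2.6, and 2.4.1 does not treat 6 months as primary.
- *A reader might count baseline as a third chance of success.* Baseline precedes allocation, so a significant difference there could not be claimed as efficacy. The fault in listing it is conceptual and adds no further error inflation.
- *A reader might take section 2.6, "We will measure the change in wellbeing, pre- and post-intervention, in terms of mean happiness scores", as a rival change-score endpoint.* The next sentence specifies a difference between groups in 3-month means, and the calculation follows that.

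The planned covariates and the handling of the 6-month result may also sit in an analysis plan that is not shown, so their absence here is no fault. Section 2.5 keeps investigators other than the data manager blind until all visits are analysed, which reduces the scope for choosing a visit by its result.

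The reply does not remove the mismatch. The one sentence that defines the primary analysis names no deciding visit and includes a visit before randomisation. An unseen document cannot change what this sentence says.

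**Conclusion.** The point holds as an inconsistency in 2.8 against a primary endpoint that is otherwise fixed at 3 months, together with the misplaced inclusion of baseline in an effect comparison. The primary endpoint is not undefined. The sample size and alpha are consistent with one 3-month test and need no change.

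The 7% to 9% familywise error is conditional. It needs 3 and 6 months to be treated as co-primary, either one to suffice at 5%, and an assumed correlation between 0.9 and 0.4. It measures what a literal reading of 2.8 would permit and is not the error rate of the trial as designed. The point is worth correcting because the deciding comparison should be unmistakable in the analysis section, but it falls below a must-fix.

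**What to change.** Replace the sentence in 2.8 with wording such as:

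*The primary analysis estimates the between-arm difference in mean AHI at 3 months (two-sided 5%), adjusted for baseline AHI. The 6-month difference is secondary. Baseline AHI is reported descriptively and is not part of the effect comparison.*

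Any separate analysis plan should use the same wording. The adjustment makes proper use of a measurement that is already collected, and it can be expected to help precision. The cost is one rewritten sentence, with no change to sample size, alpha, visits or data collection.

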*Inclusion criteria for patients:* All persons identified by the ASHA in the community with a score of 10 or above on the nine-item Patient Health Questionnaire [32] who consent to participate in the trial. *Exclusion criteria for patients:* a) children and adolescents (10–19 years of age as defined by WHO), b) patients with significant speech, hearing, language or cognitive impairment, c) patients needing urgent medical or psychiatric attention, d) patients not planning to stay in the trial location for at least 3 months after initial screening, and e) patients not understanding Hindi.

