From the standpoint of patient recruitment, all patients (of both arms) who score ≥10 on the nine-item Patient Health Questionnaire (PHQ-9) and have agreed to receive the first HAP session by the ASHA will be approached for participation in the study, and after obtaining written informed consent, the research team member will administer the baseline assessment (i.e., social and demographic information) to the patient. We will use the PHQ-9 score as assessed by the ASHA prior to starting HAP as the ‘baseline’, and the endline assessment including a repeat PHQ-9 and assessment of patient satisfaction, conducted by the research assistant after 3 months, will allow a comparison of pre- and post-HAP PHQ-9 scores, in addition to between-arm comparison of remission rates at follow-up.

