#### Randomization

2.3.4

Following the baseline assessment, ASHAs will be randomly allocated (1:1) to one of two study arms using Stata-17 [37]. Stata allows the researcher to set the ‘seed’ used to start the random number generator (RNG) process, so that it is reproducible; and it tracks the ‘state’ which the RNG is in before each command is run. Therefore, with each command, the RNG ‘state’ within the seed changes, which maintains the randomness of each subsequent command. Since we will train all ASHAs on HAP prior to randomization, any potential effects of mental health training on ASHAs' own wellbeing will be balanced between the arms. Prior to randomization, we will first stratify ASHAs who will complete baseline assessments using age (in years) and education level (number of total years of education), as these are some of the variables that may affect an ASHA's absorption of the intervention content and potentially affect the wellbeing outcome. Stratification will ensure that age- and education-distribution between the arms is balanced. Research team will inform all ASHAs (regardless of arm allocation) of the scheduled dates of their next (1-month) follow-up assessment, and so on for 3-month and 6-month follow-ups. Further, a separate research assistant will call the ASHAs and confirm their availability to attend the intervention residential workshop (if allocated to the intervention arm). ASHAs allocated to the intervention arm will receive the workshop within 7–10 days of baseline assessment.

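### Patient remission is to be tested as if patients were independent, although ASHAs are randomised and the number of patients per ASHA is not capped

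*Protocol article*

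**What the plan says.** Section 2.3.4 (Randomization) makes the health worker the unit of allocation: "ASHAs will be randomly allocated (1:1) to one of two study arms". Remission, a PHQ-9 score below 10 at three months, is measured on the patients whom those workers treat. Section 2.8 (Statistical analysis) compares it between arms "using the test of difference between two independent proportions".

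Section 2.6 (Sample size estimation) sets out to "assume rates of 40 % and 60 % in the control and intervention arm respectively". It continues "With a two-sided α of 0.05, and 80 % power", and concludes that "we will need 97 patients with depression per arm". From this it infers that "each of the 122 ASHAs per arm will be required to provide HAP sessions to at least 1 patient", with allowance for dropout and loss to follow-up.

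Patient eligibility in 2.3.1 covers "All persons identified by the ASHA in the community with a score of 10 or above on the nine-item Patient Health Questionnaire", subject to consent and the listed exclusions. Section 2.3.3 has the team approach all such patients in both arms who have agreed to a first HAP session. Neither section sets a maximum per ASHA.

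**The concern.** Patients of one ASHA share the person treating them, the village and, necessarily, the arm. For patient outcomes the design is therefore cluster-randomised with the ASHA as cluster. A two-sample test of proportions treats every patient as a separate randomised unit. Where clusters hold more than one patient and outcomes within them are positively correlated, that understates the standard error, so confidence intervals are too narrow and p-values too small.

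Secondary hypothesis (c) in 1.1, that coaching health workers improves remission among their patients, depends on this comparison. The Discussion looks for a consequent benefit to patients and communities. A nominally significant result could be less secure than it appears. Because 2.8 names the test, this is a choice already made, not a detail left to an analysis plan.

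**Working it through.** **1. Reproduce the 97.** Inputs from 2.6: 40% against 60%, two-sided α 0.05, power 80%. With the pooled null proportion of 0.5:

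n = [1.96·√(2·0.5·0.5) + 0.8416·√(0.4·0.6 + 0.6·0.4)]² / 0.20² = (1.3859 + 0.5831)² / 0.04 = 96.9, so 97 per arm.

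This matches. It is the formula for independent patients, with no design effect.

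**2. Is more than one patient per ASHA foreseen?** The only planning figure is the minimum of one. Against that:
- Sections 2.3.1 and 2.3.3 set no cap.
- The Introduction gives each ASHA a population of about 1000.
- Section 1.1 refers to each ASHA's patients in the plural.
- Table 2 compares numbers of completed patients and dropouts between arms, which presupposes that the counts vary.

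Sharing is therefore an inference, though a likely one. Its extent is not given.

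**3. Effect on the test.** With m patients per ASHA and equal clusters, DE = 1 + (m − 1)·ICC. The true standard error is √DE times the naive one, and the actual type I error is 2·[1 − Φ(1.96/√DE)]. Example: at m = 5 and ICC 0.10, DE = 1.4, √DE = 1.183, 1.96/1.183 = 1.656, and the error is 9.8%. Both m and the ICC are assumptions.

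| m | ICC 0.02 | ICC 0.05 | ICC 0.10 |
|---|---|---|---|
| 1 | 5.0% | 5.0% | 5.0% |
| 2 | 5.2% | 5.6% | 6.2% |
| 3 | 5.5% | 6.2% | 7.4% |
| 5 | 5.9% | 7.4% | 9.8% |

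For m from 2 to 5 the standard error ratio runs from 1.01 to 1.18.

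**4. Unequal clusters.** With a coefficient of variation CV of cluster size, also assumed, DE = 1 + [(1 + CV²)·m − 1]·ICC. At m = 5, ICC 0.10 and CV 0.7, DE = 1 + (1.49·5 − 1)·0.10 = 1.645 and the error is 12.7%. The same CV gives 7.0% and 9.1% at m = 3, and 8.8% at m = 5 with ICC 0.05.

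**5. Simulation.** Beta-binomial outcomes, 122 ASHAs per arm, null remission rate 40%, 40,000 replicates. Equal clusters gave 6.2% at m = 3, ICC 0.05 and 9.8% at m = 5, ICC 0.10. Moderately unequal clusters (one plus a Poisson count with mean 4, so CV = √4/5 = 0.4) gave 10.8% in the last case. The formula with CV 0.4 gives 10.7%.

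**6. Power.** Patients needed per arm, as 96.9 × DE rounded up, for ICC 0.02, 0.05 and 0.10:
- m = 2: 99, 102, 107
- m = 3: 101, 107, 117
- m = 5: 105, 117, 136

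With exactly 97 patients per arm, power would fall from 80% to between 79% and 66% over this range. But 122 ASHAs with two patients each supply 244 per arm, and power is then about 99% even at ICC 0.10. Power is threatened only if the total stays near 97 while those patients come from few ASHAs.

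**The case against.** The best defence is that 2.6 can be read as planning one patient per ASHA: 122 ASHAs per arm, less losses, leave 97 evaluable patients (25/122, about 20% lost). On that reading the named test is valid and 97 needs no design effect. Part of this stands: 97 is not a miscalculation, and the missing design effect is an error only if clusters exceed one. It does not settle the matter, because the text sets a minimum and no maximum, and no rule restricts the analysis to one patient per ASHA.

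A reader might infer that every eligible patient is enrolled, so that several patients per ASHA are a fact. The documents do not say so. Patients must agree to a first session, be approached and consent, and the minimum concerns providing HAP, not enrolment. A reader might also infer that the false-positive rate must exceed 5%. That requires both m above 1 and a positive ICC, and neither is documented. At m = 1.5 the error is only about 5.1% to 5.6% for ICC 0.02 to 0.10.

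It is also fair to say that this is one secondary outcome, and that the primary AHI comparison is made on the randomised unit, so patient clustering does not touch it.

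**Conclusion.** The point holds conditionally. The protocol fixes an independence test for an outcome nested within the randomised unit and does not limit the nesting. The test is anticonservative whenever ASHAs contribute more than one patient and the ICC is positive.

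Under assumed ICCs of 0.02 to 0.10 and two to five patients per ASHA, actual type I error is about 5.2% to 9.8% with equal clusters. The figure of about 13% needs five patients per ASHA, ICC 0.10 and a CV of about 0.7 together, so it is an upper scenario and not the expected value. The weakness lies in the validity of the inference on remission, and power is a lesser issue if most ASHAs contribute.

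No test is named for the CSQ-8 satisfaction score, so no fault is established there. The same principle would apply to any patient-level comparison of it.

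**What to change.** In 2.8, replace the two-proportion test with one of these, including all enrolled patients:
- a logistic or modified-Poisson GEE with robust standard errors clustered on ASHA; or
- a mixed logistic model with a random effect for ASHA.

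In 2.6, state that 97 per arm assumes one patient per ASHA, and give the design effect for larger clusters over a stated range of ICC and patients per ASHA. Any patient-level CSQ-8 comparison should be clustered on ASHA in the same way.

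Two additions are best left out of the main model. Batch or coach terms exist only in the intervention arm, so as fixed effects they are aliased with treatment. A partially nested random effect could serve as a sensitivity analysis. Adjustment for baseline PHQ-9 is not needed for this purpose: the ASHA, who knows her arm once allocated, makes that assessment, and it may follow randomisation.

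The cost is a change of wording and a slightly wider confidence interval. Table 3 already treats patients as linked to ASHAs by arm, so no new data are required. The change should be made before patient outcomes are compared by arm.
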